### Interim analyses {21b}

An interim analysis will be performed once half of the patients have been included (*n* = 165). Blinded data will be delivered by an independent statistician to the Data Monitoring Committee (DMC) who will then provide an allocation-blinded recommendation to the trial investigators whether to continue, hold or terminate the trial prematurely. The recommendation is based on safety and futility. Safety is based on three parameters, the number of possibly related serious adverse events, the number of early study drug discontinuations and the number of deaths within 28 days. It is difficult to provide fixed stopping criteria for safety since these events are expected to be very few, and the DMC have to assess frequency, severity and possible relationship to the study drug and give their best advice accordingly. Futility is defined as less than 5% probability of finding non-inferiority in the final analysis based on conditional power simulations as suggested by Bratton et al. [48]. The trial investigators will make the final decision whether to terminate the trial and will have to provide a written account to explain if they do not follow the recommendation from the DMC.

### Methods for additional analyses (e.g. subgroup analyses) {20b}

We will perform five sensitivity analysis to the primary outcome analysis. One will add a fixed effect (“adjust”) for the number of days of intravenous antibiotics (as a continuous variable) prior to allocation in addition to the baseline GEE model with a fixed effect for sex and a random effect for site. Secondly, we will perform an unadjusted analysis without fixed or random effects. Third, we will also analyse and report the primary outcome based on retrospective chart review versus results from the primary telephone interview. Fourth, we will also perform and report the primary outcome analysis results based on subgroups for the three different control drug allocations (i.e. ciprofloxacin, TMX and ertapenem). Lastly, we will analyse and report results for each sex separately. The last two analyses mentioned are underpowered and cannot provide base for stating individual drug non-inferiority but could provide information of interest for future trial designs.

### Methods in analysis to handle protocol non-adherence and any statistical methods to handle missing data {20c}

We will analyse the population both as intention-to-treat (ITT, i.e. as randomised), modified intention-to-treat (mITT, i.e. patient who took at least one dose of allocated study medication) and per protocol (PP, i.e. no major protocol deviations and missed a maximum of two doses of allocated study drug). We will only state non-inferiority if all three types of analyses provide concordant results [49]. If results are discordant, it will require a close examination of the data and could lead to either a statement of conditional non-inferiority or final uncertainty by the steering committee (SC).

All variables will be screened for frequency and type of missingness (i.e. missing completely at random, missing at random or missing not at random). Multiple imputation with chained equations will be used if missingness is above 5% in any variable included in the primary or secondary analysis. In the case of missingness, data with multiple imputation will be regarded as the primary analysis and complete case analysis will be performed as a sensitivity analysis.

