**Methods:**

We plan to perform an investigator-initiated non-inferiority trial. Adult hospitalised patients treated with 1–5 days of intravenous antibiotics for acute febrile urinary tract infection caused by extended spectrum beta-lactamase (ESBL) producing Enterobacterales will be randomised 1:1 to either control (7–10 days of either oral ciprofloxacin 500 mg twice daily or oral trimethoprim–sulfamethoxazole 800 mg/160 mg twice daily or intravenous ertapenem 1 g once daily, depending on sex, drug allergy, glomerular filtration rate and susceptibility testing) or intervention (10 days of pivmecillinam 400 mg three times daily and amoxicillin/clavulanic acid 500/125 mg three times daily). The primary outcome will be clinical cure 10 days (+/− 2 days) after antibiotic treatment completion. Clinical cure is defined as being alive with absence of fever and return to non-infected baseline of urinary tract symptoms without additional antibiotic treatment or re-hospitalisation (for urinary tract infection) based on a centralised allocation-blinded structured telephone interview. We plan to recruit 330 patients to achieve 90% power based on a sample size simulation analysis using a two-group comparison, one-sided alpha of 2.5%, an absolute non-inferiority margin of 10% and expecting 93% clinical cure rate and 10% loss to follow-up. The primary endpoint will be analysed using generalised estimated equations and reported as risk difference for both intention-to-treat and per protocol populations. Patients are planned to be recruited from at least 10 centres in Sweden from 2023 to 2026.

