## Sample size {14}

We expect a clinical cure rate of 93%, based on previous trials on antibiotic efficacy in febrile UTI exploring similar primary outcomes [37, 41]. We have chosen a classic absolute non-inferiority margin of 10% in accordance with the U.S. Food and Drug Administrations (FDAs) recommendation on developing new drugs for complicated UTIs [43]. We consider this to be suitable considering the low severity of all aspects of the composite primary endpoint except for 28-day mortality which we will evaluate specifically as a secondary endpoint and in the interim analysis. When using a one-sided alpha of 2.5% and performing a statistical simulation of 300 enrolled patients in 30 clinics with an intraclass correlation coefficient of 0.1 and generalised estimated equations (GEE) comparison between two groups with a random intercept for site as the primary analysis we reach 90% power. We plan on recruiting 330 patients to allow for 10% loss to follow-up. The study is not powered to infer non-inferiority between the intervention and any single antibiotic in the control group, but only towards the control group as a whole. The secondary objectives should be considered exploratory and are not based on sample size calculations.

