### Plans to promote participant retention and complete follow-up {18b}

Since the follow-up is via telephone and done centrally, we expect that retention will be high. If the central outcome assessor cannot reach the participant, they will contact the recruiting physician who will check if the participant is deceased through the medical chart. Participants who are not reported dead and still cannot to be reached for the telephone interview follow-up will not qualify for analysis of the primary outcome or bacterial culture-related outcomes but can be assessed retrospectively from medical chart review regarding 28-day mortality, which is important for the evaluation of harm. We suspect that patients who deviate from the prescribed intervention will often be categorised as a negative outcome in the primary outcome assessment (e.g. new antibiotic prescribed), while some will simply be regarded as protocol violations. However, if a participant chooses to discontinue the trial, any collected data will be discarded, and the participant will only appear as a figure in the study flow chart.

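### The per-protocol rule of at most two missed doses is stricter for PAC than for any control drug and, read plainly, excludes patients switched for failure, which weakens PP as a check on non-inferiority

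*Protocol article*

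**What the plan says.** Section {20c} names ITT, mITT and PP populations, and defines the last as "per protocol (PP, i.e. no major protocol deviations and missed a maximum of two doses of allocated study drug". The count is the same for every regimen. The decision rule follows: "We will only state non-inferiority if all three types of analyses provide concordant results". If the results disagree, the section allows the steering committee either a conditional claim of non-inferiority or a finding of uncertainty. Section {5d} says that this committee is the principal and co-principal investigator.

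The regimens have different dosing frequencies. The Abstract gives the control options, among them "intravenous ertapenem 1 g once daily", and the intervention as "pivmecillinam 400 mg three times daily and amoxicillin/clavulanic acid 500/125 mg three times daily"; TMX and ciprofloxacin are taken twice daily. Table 1 expects about 35% of controls on TMX, 25% on ciprofloxacin and 40% on ertapenem.

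Under Outcomes, additional antibiotic treatment or readmission for UTI symptoms is a primary-outcome failure. Section {11b} lets the patient or physician stop or change treatment at any time. Section {18b} expects that "patients who deviate from the prescribed intervention will often be categorised as a negative outcome in the primary outcome assessment". The article does not define a missed dose, does not say whether the two PAC drugs count as one dose or two, and does not place patients switched for failure either inside or outside PP.

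**The concern.** PP is required because non-adherence can pull the ITT difference towards zero, which in a non-inferiority trial favours the claim. For PP to guard against this, membership should mean the same in both arms and should not depend on the outcome. The two-dose rule has a problem on each count.

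First, one number of doses is applied to regimens with one, two or three dosing times a day, so PAC patients must come closer to full adherence than controls to stay in. Second, someone taken off the allocated drug because it is failing, with more than two doses still to come, has on a plain reading missed more than two doses. Removing such patients takes out failures, and takes out more of them from the worse arm. At stake is whether PP can still contradict an ITT result that is too favourable, and how a trial that passes on PP alone would be interpreted.

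**Working it through.** **The plan's own figure.** Sample size {14} uses a 93% cure rate (taken for both arms), a 10-point margin, one-sided 2.5%, and 300 patients in 30 clinics with an ICC of 0.1, and says "we reach 90% power". Ignoring site, n per arm = (1.960 + 1.282)² × 2 × 0.93 × 0.07 / 0.10² = 137. At 150 per arm the power is Φ(0.10/√(2 × 0.0651/150) − 1.96) = 92.4%. Simulating 30 clinics of 10 gives 88.9% to 93.1%, depending on how the ICC is read. The 90% is reproduced, so its inputs are used below. Evaluable patients per arm: 330 × 0.9 / 2 = 148.5, taken as 148.

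**The dose count.** Days allowed = 2 / doses per day. Share of course = 2 / scheduled study-drug doses. The shares are shown for 1–5 prior intravenous days counted inside the total, and for a full course after them. The last two columns give the doses missed and PP status.

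| Regimen | Doses/day | Days allowed | Share, IV days inside total | Share, full course | Stop 1 day early | Stop 2 days early |
|---|---|---|---|---|---|---|
| PAC, dosing times | 3 | 0.67 | 2/27 to 2/15 = 7–13% | 6.7% | 3, out | 6, out |
| PAC, each drug counted | 6 | 0.33 | 2/54 to 2/30 = 4–7% | 3.3% | 6, out | 12, out |
| TMX; ciprofloxacin in men | 2 | 1 | 2/18 to 2/10 = 11–20% | 10% | 2, in | 4, out |
| Ciprofloxacin in women | 2 | 1 | 2/12 to 2/4 = 17–50% | 14% | 2, in | 4, out |
| Ertapenem | 1 | 2 | 2/9 to 2/5 = 22–40% | 20% | 1, in | 2, in |

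With the expected control mix, the mean control allowance is 0.35 × 1 + 0.25 × 1 + 0.40 × 2 = 1.4 days, against 0.67 day for PAC.

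**Dropping failures.** Let p be the true cure rate and f the share of failures removed from PP. The documents give no value for f, so a range is shown. PP cure = p / (1 − f(1 − p)). At the margin (93% versus 83%) with f = 0.25:

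- PAC: 0.83 / (1 − 0.25 × 0.17) = 0.867
- Control: 0.93 / (1 − 0.25 × 0.07) = 0.947
- Difference: −8.0 points

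The pass rates come from simulation with a Wald 95% interval and 148 per arm, and are approximate. In the last column, 10% of each arm is assumed to cross over for reasons unrelated to failure, to take the other arm's cure rate, and to be outside PP.

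| f | PP difference | PP alone passes | ITT and PP both pass | PP passes, ITT fails | Both pass, 10% crossover |
|---|---|---|---|---|---|
| 0 | −10.0 | 3% | 3% | 0% | 2.9% |
| 0.10 | −9.2 | 5% | 2.7% | 2% | 4.0% |
| 0.25 | −8.0 | 10% | 2.7% | 7% | 5.3% |
| 0.50 | −5.7 | 34% | 2.9% | 31% | 7.3% |

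If the shares differ, with 20% of control and 40% of PAC failures dropped, the PP difference is 0.83/0.932 − 0.93/0.986 = −5.3 points. PP alone then passes in about 32% of trials, and both pass in about 3%.

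The crossover column rises because ITT is diluted. Its difference becomes (0.9 × 0.83 + 0.1 × 0.93) − (0.9 × 0.93 + 0.1 × 0.83) = 0.84 − 0.92 = −8.0 points, so ITT no longer blocks what PP lets through.

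**The case against.** The strongest reply is that PP does not decide alone. ITT keeps every randomised patient, including those switched for failure, and must also pass. A reader might infer from the PP-alone figures that the trial would make a false claim 10% or 34% of the time. The documents do not support that: without dilution the joint rate is about 3%, the same as with failures kept. This part of the reply stands.

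It also stands that removal of failures is not a stated rule. A missed dose could mean non-adherence only, and an analysis plan not available here could add an exception. Even on the strict reading, failures that arise after treatment ends, or with two or fewer doses left, stay in PP. Patients enter only after 1–5 days of active intravenous treatment and when an oral switch is judged safe, and cure is judged about 10 days after completion, so the share dropped may be small. At 10%, PP alone passes in only about 5% of trials.

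Two things do not yield. The unequal count is written into the protocol, and no reading of a missed dose makes it equal. And the joint rate stays near 3% only while ITT is undiluted, whereas dilution is the situation for which PP is required; the Discussion of this open-label trial relies on the three populations to manage part of the bias from non-blinding.

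**Conclusion.** The concern holds in a limited form. That the dose rule selects the arms differently follows from the documents alone: 0.67 day for PAC against 1 or 2 days for the control drugs. That patients switched for failure leave PP is the plain reading, with no exception stated, but it remains an inference. If it applies, PP is biased towards non-inferiority by an amount set by the assumed share: about 0.8, 2.0 or 4.3 points at 10%, 25% or 50%.

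It would go too far to say that the safeguard fails outright or that the trial's error rate is generally inflated. What is lost is PP's value as a separate check. With an assumed 10% crossover, the joint false-claim rate goes from about 2.9% to between 4.0% and 7.3%. Without crossover, the effect is trials at the margin that pass on PP but not on ITT (about 2%, 7% or 31%), which the discordance clause could turn into a conditional claim. Important, not must-fix.

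**What to change.** (a) State that a patient who meets a primary-outcome failure criterion after a prespecified minimum exposure, the same in both arms, stays in PP as a failure whatever doses follow.

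(b) Replace the two-dose count by one proportion of the scheduled study-drug course, the same for every regimen, counted up to failure or end of treatment. 80% is an example, not a figure from the protocol. State how the two PAC components are counted.

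Both are changes to analysis wording, to be made before the allocation code is revealed; treatment, visits and sample size are untouched. There are two costs. PP will admit some more partly adherent PAC patients. The number of missed doses or the stop date must also be recorded at the interview or chart review: sections {11b} and {11c} ask about timing, reasons and whether all medicines were taken, but describe no dose count. The present two-dose rule needs that count too.

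### Discordant analysis sets can still yield an undefined conditional non-inferiority claim at the steering committee's discretion, and the 90% power describes one comparison, not the concordance rule

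*Protocol article*

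**What the plan says.** Four places in the protocol article bear on the decision rule.

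- Section {20c} defines ITT, mITT and PP and says: "We will only state non-inferiority if all three types of analyses provide concordant results". For discordant results it calls for a close look at the data, which "could lead to either a statement of conditional non-inferiority or final uncertainty by the steering committee". It does not define the conditional label, name the set that must pass, or say what separates the two outcomes.
- Section {20a} declares non-inferiority from a single lower confidence bound against −10 points and names no analysis set.
- The abstract (Methods) says the primary endpoint will be "reported as risk difference for both intention-to-treat and per protocol populations". mITT is not mentioned.
- Section {14} rests on a "statistical simulation of 300 enrolled patients in 30 clinics with an intraclass correlation coefficient of 0.1", and reports that a GEE comparison of two groups "with a random intercept for site as the primary analysis we reach 90% power". It adds 10% for loss to follow-up, giving 330. It mentions neither PP exclusions nor the need to pass in more than one set.

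Section {5d} identifies the steering committee as the principal and co-principal investigator.

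**The concern.** A non-inferiority trial makes one confirmatory claim, and its error rate is known only if the rule for making that claim is fixed before the results are seen. Here the main rule is strict, but the next sentence opens a second route to a positive statement. That route is used once the data are known, by two investigators, without a criterion. Readers of the eventual report may well take conditional non-inferiority as success.

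Discordance is a realistic event. Care is open-label, and section {18b} expects patients who deviate from the allocated treatment often to be counted as failures. PP would then lose failures preferentially, which pulls the PP difference towards zero. PP could pass where ITT does not.

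The power statement is a lesser matter. A reader of {14} and {20c} together would take 90% as the chance of meeting the stated rule, but it was computed for one comparison.

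**Working it through.** **Inputs from section {14}:** 93% cure (taken as equal in both arms), margin 10 points, one-sided alpha 2.5%, 300 patients simulated, 330 recruited with 10% loss. 1:1 allocation is from section {8}. The documents give no expected PP share, so every exclusion rate below is an assumption.

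**Step 1: the plan's own figure.** Power = Φ(0.10/SE − 1.96), with SE = √(2 × 0.93 × 0.07 / n per arm).

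- 150 per arm: SE = 0.02946, 0.10/SE = 3.394, power = Φ(1.434) = 92.4%.
- 148.5 per arm (330 × 0.9 = 297): SE = 0.02961, 0.10/SE = 3.377, power = Φ(1.417) = 92.2%.
- Binomial simulation with Wald limits: 91–92%.
- Simulated GEE with 30 sites and intraclass correlation 0 or 0.1 (sex term omitted): 91.1–93.9%.

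The 90% is met for the single comparison it describes.

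**Step 2: the concordance rule and its escape route.** Simulated trials with 148 per arm and Wald 95% limits; PP nested in ITT, mITT taken as equal to ITT. Power is at 93% in both arms. Error is at 93% against 83%, a true ITT difference of −10 points.

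| Assumed PP exclusion | Power, ITT and PP both pass | Error, both pass | Error, at least one passes |
|---|---|---|---|
| None (ITT alone) | 91% | 2.9–3.0% | 2.9–3.0% |
| 10% at random | 88% | 2.1% | 3.8% |
| 20% at random | 84% | 1.8% | 4.2% |
| 30% at random | 79% | 1.5% | 4.5% |
| 20% of failures, 10% of cures | 89% | 2.3% | 5.6% |
| 30% of failures, 10% of cures | 89% | 2.5% | 8.9% |
| 50% of failures, 10% of cures | 91% | 2.7% | 25% |
| 50% of failures, no cures | 91% | 2.8% | 34% |

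ITT alone lies slightly above 2.5% because the Wald limit is a little liberal at these rates.

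**Step 3: why selective exclusion matters.** Cure in PP = p(1 − c) / [p(1 − c) + (1 − p)(1 − f)], where f and c are the excluded shares of failures and cures. With f = 0.30 and c = 0.10:

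- p = 0.93: 0.837/0.886 = 94.5%.
- p = 0.83: 0.747/0.866 = 86.3%.

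The true PP difference is −8.2 points while the true ITT difference is −10. The PP set is inside the margin by selection alone.

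**Step 4: cross-check with three separate sets.** With 300 evaluable patients, mITT at 95–98% of ITT and random exclusion, power to pass all three sets is 89.5%, 87.8%, 86.8%, 84.6% and 79.3% at PP shares of 95%, 90%, 85%, 80% and 70%. If patients outside PP cure at only 80%, it is about 90% at PP shares of 80–95%.

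**The case against.** The strongest reply is that {20c} does not break its own rule. It withholds the plain label when sets disagree and offers a different, qualified one, or a finding of uncertainty. A reader might infer a flat self-contradiction, or that the effective rule is success in any one set. The text supports neither: it says discordance could lead to such a statement and makes nothing automatic. The unqualified claim stays conservative, with error no higher than for ITT alone in every scenario above.

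A reader might also put the largest error (25–34%) beside the lowest power (79%). They cannot occur together. The scenarios giving 25–34% keep joint power at about 91%, and those cutting power to 79–88% leave the at-least-one-set error near 4%. The 25–34% rests on PP losing half of all failures, which nothing in the documents supports as a quantity. Section {18b} supports the direction only.

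The 90% in {14} is not wrong: it is tied to one comparison and is reproduced. The abstract lists what will be reported and need not be read as a decision rule.

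Finally, section {17a} keeps the arms coded until the endpoints have been evaluated. This helps, but the text does not place the discordance judgement before the code is broken, and coding does not hide which sets pass under each possible labelling.

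What the reply leaves standing is the discretionary route itself. A separate analysis plan may hold further detail, but one that removed this route would conflict with the protocol as written.

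**Conclusion.** The point holds as a defect in how the claim is fixed, not as a proven breach of the 2.5% level. The protocol states a route to a positive, undefined conclusion, open after the results are known and governed by no criterion. Section {20a} adds a single-bound rule that names no set.

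The error figures apply only if the conditional label is counted as success whenever one set passes. On that reading, error is about 4% under random PP exclusion of 10–30%, and about 6–9% if PP drops 20–30% of failures and 10% of cures, against about 3% for ITT alone.

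The power issue is one of disclosure. The concordance rule has about 79–88% power under random exclusion of 10–30%, and about 89–91% if exclusions are mainly failures. With no PP share in the documents, no single figure can replace 90%. Nor do the figures show that the trial is too small for the comparison it was sized on.

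**What to change.** - **Section {20c}:** delete the conditional statement. Say that if the lower 95% limit is not above −10 points in every deciding set, non-inferiority is not demonstrated, and that discordance between sets will be described and discussed without a claim. Keep the stated ITT, mITT and PP requirement; no defect in mITT has been shown that would justify dropping it.
- **Section {20a} and the abstract:** name the same three sets, so that one rule appears throughout.
- **Section {14}:** say that 90% is the power of the single primary comparison, and give the power of the joint rule over an explicit range of assumed PP exclusion, both random and concentrated in failures.

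The cost is an amendment of wording and a slightly less favourable power statement. Enrolment does not change. The amendment should be made before any comparative results are seen.
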